### Statistical analysis

As described in the study protocol for the RCTs, the main analysis will be carried out according to the intention-to-treat (ITT) principle, that is, all participants will be analyzed according to the arm they were randomly assigned to [23]. In alignment, our health economic evaluations will also follow the ITT approach.

Descriptive analysis and statistical tests for the comparison of differences in baseline variables between the groups will be performed. Depending on the type and distribution of the variables (e.g., resource utilization, HSUV, loneliness, capability), different statistical methods will be applied. Normally-distributed continuous variables will be compared by analyzing their means and standard deviations using parametric test procedures, such as the Students t-test [82, 83]. Non-normally distributed continuous variables will be analyzed using non-parametric tests, such as the Mann-Whitney U test, focusing on medians and interquartile ranges [82, 83]. Categorical variables will be compared using the chi-square test [84]. All tests will be two-sided with a significance level set at α = 0.05.

Health effects and costs will be reported as mean differences to be used in the cost-utility/ -effectiveness/ and -capability analysis [85]. To account for the typically skewed distribution of cost and outcome data, regression-based methods, primarily ordinary least squares, combined with non-parametric bootstrapping will be used to estimate mean differences and corresponding confidence intervals without relying on parametric assumptions [86–90]. If the data exhibit extreme skewness or if bootstrapping is deemed unsuitable, alternative methods will be explored. In line with current recommendations, generalized linear models may be applied as an alternative analytical strategy where appropriate [89]. In the presence of significant differences in baseline characteristics between the groups, such as in socio-demographic factors or utility values, adjustment will be made by using multivariable regression-based methods [27, 86].

In case of outliers in cost data, winsorizing will be applied in sensitivity analyses [91, 92]. Outliers will be classified using the interquartile range (IQR). Values lying outside a range of 1.5 times IQR above the 75th percentile or below the 25th percentile will be defined as outliers [91]. Outliers will be replaced with the largest or smallest value not considering the outliers [91]. In case of strong correlation between costs and health outcomes [93], seemingly unrelated regression models to jointly analyze costs and health outcomes will be applied in sensitivity analyses [94].

RStudio and SAS software (SAS Institute Inc) will be used for statistical analyses [95].

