*EQ-5D-5L* European Quality of Life 5 Dimensions 5 Level, *HRQoL* Health-related quality of life

The EQ-5D-5L questionnaire assesses five dimensions mobility, self-care, usual activities, pain/ discomfort, and anxiety/ depression with respectively five levels to be indicated by the respondents (no problems, slight problems, moderate problems, severe problems, and extreme problems) resulting in 3,125 health states [50]. A health-state utility value (HSUV) is attached to each of these specific health states. Utilities are a preference-based single number index ranging between 0 (dead) and 1 (perfect health). Quality-adjusted life years (QALYs) are derived by weighting the time in a health state by the HSUV, that is multiplying the HSUV with the time each individual is in the health state [50] and calculating the area under the empirical utility curve for the exact time until the final follow-up after twelve months or death. The EQ-5D-5L questionnaire will be distributed to and filled out by the participants in Barcelona and Prague. However, in Helsinki, the EQ-5D-5L questionnaire will be used as a proxy version filled out by facilitators or study nurses. The proxy questionnaire is provided for participants who are unable to answer the original questionnaire due to cognitive impairments.

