As the EQ-5D-5L questionnaire is used to value a person’s health-related quality of life but might not capture all aspects of social well-being, we will perform an additional cost-capability analysis (CCA). Therefore, the ICECAP-A questionnaire will be used. The ICECAP-A questionnaire comprises additional aspects of well-being including dimensions beyond mere health and such as attachment, stability, achievement, enjoyment, and autonomy [31, 55]. These five dimensions are assessed on four levels resulting in a total of 1,024 capability states. For ICECAP-A, different value set exists [56–59]. We will use the original UK tariff as referred to by the University of Bristol [60]. After scoring a value for each of the five dimensions, the value for the overall capability state is calculated by summing them up. A capability state can have a value from 0 (no capability) to 1 (full capability). By multiplying capability values with the dwelling time in the capability state, years of full capability (YFC) are calculated [57]. The approach for calculating YFC is similar to calculating QALYs, however capability states are used instead of health states. The ICECAP-A questionnaire will be included in the trials in Barcelona and Prague.

Data from the EQ-5D-5 L [61], the DJGLS [52], and the ICECAP-A questionnaire [31] are collected at t0, t1, t2, and t3.

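### Baseline adjustment depends on a significant baseline test, which costs precision and leaves avoidable chance error in the QALY, LFD and YFC differences

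*Protocol article*

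**What the plan says.** The rule is in the *Statistical analysis* section of the protocol article. It first plans baseline comparisons: "Descriptive analysis and statistical tests for the comparison of differences in baseline variables between the groups will be performed". It sets their level: "All tests will be two-sided with a significance level set at α = 0.05". Mean differences in cost and effect are then to be estimated as follows: "regression-based methods, primarily ordinary least squares, combined with non-parametric bootstrapping will be used to estimate mean differences". No covariate is named as always included. Covariates enter through one sentence: "In the presence of significant differences in baseline characteristics between the groups, such as in socio-demographic factors or utility values, adjustment will be made".

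Table 4 defines each increment as a plain difference of arm means. Nothing elsewhere in the article commits to adjustment regardless of the baseline tests.

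The outcomes are built from t0 onwards. For QALYs, the *Measurement and valuation of outcomes/ benefits* section specifies "calculating the area under the empirical utility curve for the exact time until the final follow-up after twelve months or death". For YFC it says: "The approach for calculating YFC is similar to calculating QALYs, however capability states are used instead of health states". The LFD example in Appendix A1 averages the t0 and t1 values over the first 90 days, so baseline enters there too.

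**The concern.** After randomisation, any baseline difference between arms is due to chance. A p-value for that difference does not show whether the covariate is worth adjusting for. What matters is how strongly the covariate predicts the outcome, and baseline utility predicts a QALY strongly because it is a component of it.

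Making adjustment wait for significance has three consequences:

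- The base case will nearly always ignore the best available predictor, in an analysis that the *Sample size and missing data* section concedes may be underpowered.
- When a moderate but non-significant gap occurs, the estimate carries it although it could have been removed.
- The covariate set is unknown until the data are seen, which sits badly with the article's stated aim of a transparent, reproducible process.

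The trigger can also look at the wrong quantity. For non-normal variables the planned test is Mann-Whitney with a focus on medians, whereas the QALY difference depends on means.

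**Working it through.** **Inputs from the article.** Visits are at 0, 3, 6 and 12 months. There are 316 participants per trial, allowing for 25% drop-out. Baseline tests are two-sided at 0.05. The thresholds used below are EUR 25,000 per QALY (one of the Spanish figures quoted) and CZK 1.2 million per QALY.

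**Assumptions, because the article gives no values.** Allocation is 1:1, utility SD is 0.20 (range 0.15–0.25), any two visits have the same correlation r (0.3, 0.5 or 0.7), the data are normal and the baseline trigger is a t-test.

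**Reproducing the article's figures.** 118/(1 − 0.25) = 157.3, rounded up to 158 per arm, or 316 in total, so about 118 per arm are evaluable. The LFD example also reproduces: 90×0 + 90×0.2 + 180×0.7 = 144.

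**1. Weight of baseline.** Trapezoid weights in years are 0.125, 0.25, 0.375 and 0.25. For LFD the t0 weight is 45 of 360 days, which is again 0.125.

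**2. Slope of the QALY on baseline utility.** b = 0.125 + 0.875r, giving 0.3875, 0.5625 and 0.7375.

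**3. Largest gap that passes as non-significant.** 1.96×√(2/118) = 0.255 SD, or 0.051 utility at SD 0.20. With 158 per arm it is 0.221 SD, or 0.044.

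**4. Shift in the unadjusted QALY difference, 118 per arm.**

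| r | Largest non-significant gap | Median gap (0.6745 SE) |
|---|---|---|
| 0.3 | 0.3875×0.051 = 0.020 | 0.007 |
| 0.5 | 0.5625×0.051 = 0.029 | 0.010 |
| 0.7 | 0.7375×0.051 = 0.038 | 0.013 |

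The ratio of the two columns is 0.6745/1.96 = 0.34. Over SD 0.15–0.25 and all three correlations, the edge value runs from 0.015 to 0.047. At r = 0.5 the edge value (0.0287) is worth about EUR 720 (0.0287×25,000) or CZK 34,000 (0.0287×1,200,000) per participant. For LFD, with an assumed SD of 0.30–0.35 on the 0–1 loneliness value, the edge shift is 0.255×SD×(45 + 315r), or about 11–24 days.

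**5. Precision against the stated rule.** Let k = 2×0.20²/118 and Σw² = 0.28125.

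- Never adjusting: variance = k[Σw² + r(1 − Σw²)].
- Always adjusting: the same minus k·b².
- Test, then adjust: the always-adjusted variance plus k·b²×0.721. Here 0.721 = 0.95 − 2×1.96×φ(1.96) is the part of the baseline variance that falls in the non-significant region (φ is the standard normal density).

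| r | SE, stated rule | SE, always adjusted | Variance ratio | SE reduction |
|---|---|---|---|---|
| 0.3 | 0.0176 | 0.0153 | 1.31 | 13% |
| 0.5 | 0.0194 | 0.0148 | 1.70 | 23% |
| 0.7 | 0.0207 | 0.0128 | 2.63 | 38% |

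A simulation of 8,000 trials per setting, with no treatment effect, gave variance ratios of 1.30, 1.77 and 2.66 and SE reductions of about 12%, 25% and 39%. These agree with the formula apart from simulation error.

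**6. Behaviour of the rule in that simulation.** The baseline test was non-significant in about 95% of trials. When the baseline z lay between 1 and the significance limit, the mean error of the stated rule was 0.013, 0.020 and 0.026 QALY, against about 0 with adjustment. Type I error in that subset was 6.6–8.9%, against about 4.5%. Over all trials the rule was conservative, at 2.9–4.2%.

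**The case against.** The strongest defence is that randomisation makes the unadjusted difference unbiased, and that the planned bootstrap intervals and acceptability curves already reflect chance imbalance as sampling error. That stands. A reader might infer a systematically wrong or anti-conservative cost-utility ratio, but the documents do not support this: over all randomisations the rule is unbiased and conservative.

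Four further limits also stand:

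- A reader might claim an SE gain of 29–45% at r = 0.5–0.7. That compares adjustment with never adjusting, whereas the stated rule does adjust in the most imbalanced trials. The fair gain is the smaller one above.
- The 0.020–0.038 shift is the edge case at p = 0.05. Only about 1 trial in 20 has a gap that large or larger.
- A reader might infer that imbalance could match the treatment effect and reverse the conclusion. The article states no expected QALY effect or incremental cost, so this cannot be shown. It also reports no threshold for Finland, none established for LFD and none official for YFC.
- Baseline cost is not overlooked. The list of adjusters is only illustrative, and resource use is among the variables the section names for its statistical methods. Its adjustment would simply be conditional as well.

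Finally, the adjustment sentence does not itself give a p-value, so its trigger word could mean a relevant difference. With baseline tests at 0.05 in the same section, statistical significance is the natural reading. The looser reading would still leave a data-dependent rule, with no threshold.

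**Conclusion.** The point holds as one of efficiency and prespecification. The article states a conditional rule, so this is not a detail left to an analysis plan, and nothing else in it overrides the rule. The rule gives up roughly an eighth to two fifths of the attainable reduction-free SE: under the assumptions above, always adjusting would cut the SE of the QALY difference by about 12–13% at r = 0.3, 23–25% at r = 0.5 and 38–39% at r = 0.7. It also leaves conditional error of up to about 0.020–0.038 QALY, and typically about a third of that.

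The sizes rest on the assumed SD, correlation, equal allocation and 118 per arm, and one SD is applied to three different populations, including proxy-rated residents in Helsinki. The direction does not depend on these values as long as baseline predicts the outcome. YFC behaves like the QALY because it has the same time weights. The randomised comparison and the overall validity of the intervals are not in question.

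**What to change.** Remove the significance trigger. Baseline tables can remain descriptive. In each site's base case, prespecify these models, whatever the baseline data show:

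- QALYs on arm plus baseline utility (all three sites);
- LFD on arm plus the baseline DJGLS loneliness value (all three sites);
- 12-month cost on arm plus t0 cost or resource use (all three sites);
- YFC on arm plus baseline ICECAP-A, in Barcelona and Prague only, because Helsinki does not collect ICECAP-A.

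Refit the model in each bootstrap replicate, so that the planes, intervals and acceptability curves come from the adjusted estimates. Further prognostic covariates such as age and sex are optional, but should be named in advance if used. The unadjusted differences can be kept as a sensitivity analysis.

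The cost is a change of wording and a small change to the analysis code. The required covariates are already scheduled at t0 in Tables 1 and 3 for the sites where they are needed.

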### Sample size and missing data

The sample size for the clinical trials was determined based on detecting a significant difference in the main clinical outcome, HRQoL, measured by the 15D instrument [27, 90, 96]. The calculated sample size for each RCT is 316 patients, accounting for a potential 25% drop-out rate. The recruitment of participants was completed at the Barcelona study site in May 2024 and in Helsinki in September 2023. In Prague, 95% of participants were recruited by September 2024. Successfully recruited participants were randomized to an intervention and control group. For details of the sample size calculation, we refer to the study protocol of the RCTs of the RECETAS project [23]. Our health economic analyses are not based on sample size calculations and may, therefore, be underpowered. To assess uncertainty, we will use bootstrap-based confidence intervals (CIs) and cost-utility/ -effectiveness/ -capability acceptability curves (CUAC, CEAC, CCAC). Missing data must be treated carefully in economic evaluations [97]. Appropriate imputation approaches will be used [98]. Incompleteness in baseline data, including but not limited to age, HSUVs, loneliness, or capability, will be solved with multiple imputation [98]. For missing values during follow-up, imputation methods depending on nature of the variable, the mechanism of missingness and the percentage of missing values will be used [99]. For instance, linear interpolation (e.g., for missing in-between utilities), single imputation methods, such as the last value carry forward method (e.g., medication dose or long-term medication) [98], or multiple imputation (MI) methods such as the imputation chained equations method (MICE) will be used for skewed data (e.g., resource utilization) [98]. In case of missing at random, MI or likelihood-based methods are recommended [98]. For data missing completely at random, MI or inverse probability weighting can be applied and sensitivity analysis should be applied to test the impact of data being missing not at random [76, 98]. In case of informative censoring due to loss-to-follow-up, inverse-probability of censoring weights will be applied adjusting for covariates to control for informative censoring [89, 100].

### Health economic evaluation: CUA, CEA, and CCA alongside the trial

A comprehensive health economic evaluation, assessing differences in costs and health outcomes between the compared strategies will be conducted. These analyses will be conducted separately for each RECETAS trial site, based on the original individual data from the participants collected in Barcelona, Prague, and Helsinki. A pooled analysis will not be performed as primary analysis due to country-specific differences and target population [27]. However, it may be performed as an additional exploratory analysis depending on the characteristics of included participants to assess heterogeneity aspects and inform further research. Depending on the outcome measure, three different types of health-economic evaluations will be conducted to compare the “NBSP” strategy against the “No NBSP” strategy. The results of the health economic evaluations, which are incremental ratios as explained in Table 4, will compare the incremental costs to the incremental health outcome measures. The primary evaluation will be a cost-utility analysis using health-related utilities derived from EQ-5D-5L as health outcome measure. The incremental cost-utility ratio (ICUR) will be reported as the cost per QALY gained and reflects the ratio between the difference in costs and the difference in QALYs $$\:\mathrm{(ICUR}\;=\frac{\triangle \mathrm{Costs}}{\triangle \mathrm{QALYs}}\mathrm{)}$$. The second health economic evaluation will be performed in the form of a cost-effectiveness analysis evaluating the cost effectiveness in natural units of the clinical endpoints of the study. The incremental cost-effectiveness ratio (ICER) is the ratio of the difference in costs between the two strategies to the difference in effectiveness of the two strategies. For the CEA, we will use the change in loneliness as measured in LFDs with the DJGLS as outcome of effectiveness. By dividing the incremental costs with the incremental change in effectiveness, the ICER will be reported as the cost per LFDs $$\:\mathrm{(ICER}\;=\frac{\triangle \mathrm{Costs}}{\triangle \mathrm{LFD}}\mathrm{)}$$. In addition, a responder analysis will be conducted [32, 33]. A responder will be defined as a participant achieving a reduction of two points or more on the DJGLS at least once within the 12-month follow-up period. Responder rates will be compared between the intervention and usual care groups, and incremental costs per additional responder ($${\mathrm{Responder}\;\mathrm{rate}}\;=\frac{\triangle \mathrm{Costs}}{\triangle \mathrm{Responders}}$$) will be estimated. Uncertainty will be assessed using non-parametric bootstrapping and presented as CEAC.

Lastly, a cost-capability analysis will be applied using the differences in years of full capability derived from the ICECAP-A questionnaire as effectiveness measure. Based on the principle for calculating the ICER and the ICUR, the incremental cost-capability ratio (ICCR) will be calculated to report the cost per YFC gained $$\:\mathrm{(ICCR}\;=\frac{\triangle \mathrm{Costs}}{\triangle \mathrm{YFC}}\mathrm{)}$$. The analytic time horizon of the analyses is twelve months, aligning with the time horizon of the RECETAS trials.

**Table 4 Tab4:** Overview of calculated incremental cost-utility, cost-effectiveness, and cost-capability ratios

	Incremental Costs (in EUR or CZK)	Incremental Effectiveness	Incremental Ratio
ICUR (EUR or CZK per QALYs gained)	$$\triangle \mathrm{Costs}\;=\;\mathrm{Mean}\;\mathrm{Costs}_{\mathrm{NBSP}}-\mathrm{mean}\;{\mathrm{Costs}}_{\mathrm{UC}}$$	$$\triangle \mathrm{QALYs}\;=\mathrm{Mean}\;\mathrm{QALYs}_{\mathrm{NBSP}}-\mathrm{mean}\;{\mathrm{QALYs}}_{\mathrm{UC}}$$	$$\:\mathrm{ICUR}\text{}\mathrm{=}\frac{\triangle \mathrm{Costs}}{\triangle \mathrm{QALYs}}$$
ICER (EUR or CZK per loneliness reduced)	$$\triangle \mathrm{Costs}\;=\;\mathrm{Mean}\;\mathrm{Costs}_{\mathrm{NBSP}}-\;\mathrm{mean}{\mathrm{Costs}}_{\mathrm{UC}}$$	$$\triangle \mathrm{LFD}=\mathrm{Mean}\;\mathrm{LFD}_{\mathrm{NBSP}}-\mathrm{mean}\;\mathrm{LFD}_{\mathrm{UC}}$$	$$\:\mathrm{ICUR=}\frac{\triangle \mathrm{Costs}}{\triangle \mathrm{LFD}}$$
ICCR (EUR or CZK per YFC gained)	$$\triangle \text{ Costs}\;=\mathrm{Mean}\;\mathrm{Costs}_{\mathrm{NBSP}}-\mathrm{mean}\;\mathrm{Costs}_{\mathrm{UC}}$$	$$\triangle \mathrm{YFC}=\mathrm{Mean}\;\mathrm{YFC}_{\mathrm{NBSP}}-\mathrm{mean}\;\mathrm{YFC}_{\mathrm{UC}}$$	$$\mathrm{ICUR=}\frac{\triangle \mathrm{Costs}}{\triangle \mathrm{YFC}}$$

*CZK* Czech Koruna, *EUR* Euro, *ICCR* Incremental cost-capability ratio, *ICER* Incremental cost-effectiveness ratio, *ICUR* Incremental cost-utility ratio, *NBSP* Nature-based social prescribing, *QALYs* Quality-adjusted life years, *UC* Usual care, *YFC* Years of full capability

The results of the economic evaluations will be shown in cost-utility, cost-effectiveness, and cost-capability planes, consisting of four quadrants representing the difference of effectiveness between the strategies on the x-axis and the difference in costs on the y-axis [101]. Before the calculation of the incremental ratios (i.e., ICUR, ICER, ICCR), dominance will be evaluated. A more effective and less costly strategy is called dominant and should be implemented. A dominated strategy or technology provides less benefits at higher costs and should be discarded. No incremental ratios will be calculated for dominant or dominated strategies [102]. Results will be interpreted with priority given first to the ICUR, followed by the ICER, and, finally, the ICCR.

### Uncertainty analyses

It is recommended that economic evaluations alongside the trial address uncertainty around the cost effectiveness [27]. For this purpose, scenario and sensitivity analyses will be performed. Scenario analysis will be performed to assess the robustness of the cost-utility, cost-effectiveness, and cost-capability results. Alternative cost assumptions, including scenarios where fixed costs to set-up the program are excluded and analyses without imputation will be conducted. For sensitivity analyses, the nonparametric bootstrap method will be used with 10,000 replications on the individual-level RECETAS data set [103]. The results of the sensitivity analyses will be presented as a scatter plot and 95% confidence ellipses on the cost-utility, cost-effectiveness, and cost-capability planes. The 95% CIs for bootstrap simulations will be determined using the percentile method [104]. Uncertainty related to further parameterized assumptions will be assessed via probabilistic sensitivity analyses.

Decisions on cost effectiveness often depend on willingness-to-pay (WTP) thresholds. The incremental ratios can be compared to the relevant WTP threshold for an additional effectiveness unit determined by the responsible decision-making authority. The intervention, that is NBSP, can be identified to be cost effective if the incremental ratio is below the specific WTP. However, only few countries have an explicit WTP threshold. For example, Schwarzer et al. describe WTP thresholds in ten countries and identified only the United Kingdom and Thailand as having an explicit WTP threshold value [105, 106]. For the Spanish National Health System, estimates of such WTP thresholds range between 21,000 Euro and 24,000 Euro [107] or 25,000 Euro and 60,000 Euro [108] per QALY gained for being cost effective. In Czech Republic, a WTP threshold of 1.2 million CZK/QALY (approx. 47,000 Euro/QALY) is recommended by the State Institute for Drug Control [73]. Finnish national guidelines do not report a WTP threshold [74].

No established WTP threshold currently exists for the outcome of our CEA expressed as changes in loneliness. Therefore, results will be presented without applying a predefined threshold and interpreted in terms of relative cost-effectiveness and uncertainty (e.g., using cost-effectiveness acceptability curves).

No official WTP threshold is defined for the ICCR or the YFC. In the UK, the current discussed thresholds range from £33,500 (approx. 39,214 Euro) to £36,150 (approx. 42,316 Euro) per YFC gained [109]. However, for the ICCR there is no official predefined WTP threshold for Spain, Czech Republic, and Finland that can be used for a NBSP intervention. In order to show the probability of being cost-effective, CEAC will be presented to summarize the parameterized uncertainty regarding the cost effectiveness and to show graphically the probability of the NBSP intervention being cost effective by considering different thresholds [104].

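### The rule that NBSP is cost effective when the ratio is below the WTP gives the opposite verdict when NBSP is cheaper but less effective

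*Protocol article*

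**What the plan says.** All references are to the Protocol article.

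- *Uncertainty analyses* introduces the threshold comparison: "The incremental ratios can be compared to the relevant WTP threshold for an additional effectiveness unit determined by the responsible decision-making authority". The decision rule follows: "The intervention, that is NBSP, can be identified to be cost effective if the incremental ratio is below the specific WTP". The rule itself is not limited to any quadrant.
- *Health economic evaluation: CUA, CEA, and CCA alongside the trial* describes planes "consisting of four quadrants representing the difference of effectiveness between the strategies on the x-axis and the difference in costs on the y-axis". It checks dominance first and then states: "No incremental ratios will be calculated for dominant or dominated strategies".
- *Uncertainty analyses* also plans the bootstrap: "the nonparametric bootstrap method will be used with 10,000 replications on the individual-level RECETAS data set". On intervals it says "The 95% CIs for bootstrap simulations will be determined using the percentile method", without naming the quantity. Acceptability curves are to show the probability that NBSP is cost effective over a range of thresholds.
- Net benefit is not mentioned, and no section gives a rule for a result in which NBSP costs less and achieves less.

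**The concern.** The dominance step removes two of the four quadrants: NBSP cheaper and better, and NBSP dearer and worse. A ratio is still calculated in the other two. In one, NBSP costs more and achieves more, and the ratio is the price of a unit gained, so low is good. In the other, NBSP costs less and achieves less, and the ratio is the saving per unit given up, so high is good. Both ratios are positive, and the printed rule treats them alike.

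Read literally, the rule would report a loss of health in return for too small a saving as cost effective, and would reject a saving large enough to justify the loss. The cost-utility analysis is the primary evaluation and has published thresholds to compare against, so the rule matters most there.

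**Working it through.** **Inputs from the article.** The thresholds under *Uncertainty analyses*: for Spain EUR 21,000 to 24,000 or EUR 25,000 to 60,000 per QALY; for the Czech Republic CZK 1.2 million, given as about EUR 47,000. The article states no numerical result for the rule, so there is no figure to reproduce.

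**Algebra, with no assumed data.** Let λ be the threshold, ΔE the difference in effect and ΔC the difference in cost (NBSP minus usual care). Net benefit is NB = λ·ΔE − ΔC, and NBSP is worth its cost when NB > 0.

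- If ΔE > 0: ΔC/ΔE < λ ⇔ ΔC < λ·ΔE ⇔ NB > 0. The rule is right.
- If ΔE < 0, multiplying by ΔE turns the inequality: ΔC/ΔE < λ ⇔ ΔC > λ·ΔE ⇔ NB < 0. The rule is the negation of the right answer.

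A check on 400,000 simulated pairs at λ = 21,000 and 60,000 gave the same result: 100% agreement between rule and net benefit where NBSP is dearer and better, 0% where it is cheaper and worse.

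**Two illustrative results, cheaper and worse.**

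- A: ΔC = −100, ΔQALY = −0.02, ratio = −100/−0.02 = 5,000.
- B: ΔC = −1,000, ΔQALY = −0.02, ratio = −1,000/−0.02 = 50,000.

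| λ (EUR/QALY) | A by the rule | A: NB = −0.02λ + 100 | B by the rule | B: NB = −0.02λ + 1,000 |
|---|---|---|---|---|
| 21,000 | cost effective | −320 | not | +580 |
| 24,000 | cost effective | −380 | not | +520 |
| 25,000 | cost effective | −400 | not | +500 |
| 47,000 | cost effective | −840 | not | +60 |
| 60,000 | cost effective | −1,100 | cost effective | −200 |

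The rule and the sign of net benefit disagree in every cell.

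**What this could do to an acceptability curve.** The article gives no SDs or expected differences, so these are assumptions: 118 per arm (316 × 0.75 = 237 completers, about half per arm), SD of QALYs 0.15 with SD of cost EUR 1,500, or 0.20 with EUR 3,000, ΔQALY 0 to 0.08, ΔC −200 or +300, independent normal replicates, λ = 25,000.

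- Over these settings the cheaper-and-worse quadrant holds from 0% to about 43% of replicates.
- At ΔQALY 0.01, ΔC +300 and the larger SDs it holds 8%. The probability of positive net benefit is 0.47. Counting every ratio below λ gives 0.78. Settling dominance replicate by replicate, but leaving this quadrant unreversed, gives 0.50.
- With dominance settled per replicate, the error over all settings runs from −0.01 (0.805 against 0.816) to +0.11 (0.758 against 0.646).
- At ΔQALY 0.08 there is no difference (0.987 against 0.987 with ΔC +300 and the larger SDs).

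**The case against.** The wording around the rule points to gains: the threshold is for an additional unit of effect, and the Spanish figures are per QALY gained. The *Discussion* hypothesises that NBSP is more effective, with savings that only partly offset its delivery cost, which is the quadrant where the rule works. A cheaper-and-worse point estimate would also be visible on the plane. The reach is limited too: no threshold is applied to loneliness, none is official for years of full capability, and the Finnish guidelines report none. The comparison therefore mainly concerns the QALY analyses in Barcelona and Prague.

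This lowers the severity but does not remove the point. The decision sentence carries no restriction, and the dominance sentence shows which quadrants were treated separately. *Sample size and missing data* concedes that the economic analyses may be underpowered, so a rule that works only for the hoped-for result is not enough.

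Three stronger readings are tempting, and the article does not support them.

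- A reader might infer that percentile limits will be put on the ratio, which would have no clear meaning when replicates cross quadrants. The sentence names no quantity, and *Statistical analysis* ties bootstrap intervals to mean differences. This is an ambiguity, not a stated error.
- A reader might infer that the plan expects small effects or a net saving, which would make the reversal likely. The article does not say so; partial offset implies a net cost.
- A reader might infer that the acceptability curves will be built by counting ratios below the threshold. How they are built is not stated, and where dominance is settled per replicate the errors partly cancel.

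**Conclusion.** The printed rule is wrong for a less costly, less effective result, and nothing elsewhere in the article corrects it. That conclusion follows from algebra alone. It is a stated rule that gives a wrong answer, not a detail left to an analysis plan.

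Its practical size cannot be fixed from the article. It ranges from nothing, when the effect is clearly positive, to a reversed conclusion, if a site's point estimate lands in that quadrant. The replicate shares and probabilities above rest on assumed SDs, differences and zero correlation, and serve only as illustration. This should be fixed; it is not a must-fix.

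**What to change.** Replace the decision sentence with: NBSP is cost effective at threshold λ if λ·ΔE − ΔC > 0. Equivalently, the ratio lies below λ when ΔE is positive, and above λ when both differences are negative. State that the acceptability curves are the share of bootstrap replicates with positive net benefit at each λ.

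As a clarification only, say that the percentile intervals apply to ΔC, ΔE and net benefit.

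The cost is a few sentences of text. No new data are needed, and the planned 10,000 bootstrap replicates already supply ΔC and ΔE.
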